Numerous studies have confirmed that an improper inspiratory flow rate—too low or too high—can hinder drug delivery (3, 10). The most commonly used parameter for assessing the inhalation technique is peak inspiratory flow rate (PIFr); it is the maximum flow rate generated by a patient during inhalation to overcome the internal resistance of an inhaler (6). Different types of inhalers, such as pressurized metered dose inhaler (pMDI), dry powder inhaler (DPI), and soft mist inhaler (SMI), have varying PIFr requirements because of varied drug particle release mechanisms and device resistance. The optimal inspiratory flow rate for DPIs is approximately 60 L/min, which generates turbulence inside the device, facilitating the dispersion of the powder into fine particles that can be carried into the airways via airflow (11). In contrast, pMDIs and SMIs do not rely on the patient's active inhalation to generate turbulence for drug particle release and thus have an optimal inspiratory flow rate of about 30 L/min (12). If a patient's measured PIFr is suboptimal, it may limit medication delivery to the lower airways, thereby reducing efficacy (13). In addition to inspiratory flow rate, proper inhalation techniques are crucial for drug deposition. Adequate exhalation before inhalation minimizes residual volume, increasing the volume of medicated air inhaled and enhancing drug delivery to small airways. Furthermore, prolonging breath-holding after inhalation facilitates the deposition of fine drug particles in small airways via Brownian motion, reducing the proportion of exhaled suspended particles (14).

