### Study population and recruitment

2.2

All patients will undergo initial screening by physicians in the Department of Respiratory and Critical Care Medicine to confirm AECOPD diagnoses. Independent researchers will then conduct a secondary screening according to inclusion and exclusion criteria (Table 2) to ensure that only eligible patients are included. Patients or their legal guardians will be required to provide informed consent to participate.

**Table 2 T2:** Inclusion, exclusion, and withdrawal criteria.

**Inclusion criteria**	**Exclusion criteria**	**Withdrawal criteria**
(1) A previous pulmonary function test confirming a COPD diagnosis (postbronchodilator FEV1/FVC < 0.7) and currently hospitalization due to AECOPD	(1) Severe cognitive impairment; inability to understand assessments or instructions; and inability to comprehend the study's nature, scope, and potential consequences	(1) Hospitalization and receipt of treatment for non-AECOPD pulmonary diseases (e.g., lung volume reduction surgery, severe chest trauma) within 12 weeks after discharge
(2) Age = 40–85 years	(2) Bronchiectasis as the primary COPD manifestation	(2) Voluntary request to withdraw from the intervention or terminate follow-up observations
(3) Hospitalized patients with AECOPD who no longer meet GOLD 2025 criteria for respiratory failure or ventilatory failure.	(3) Complication due to malignancy	
(4) Continual, regular use of a fixed bronchodilator inhaler for >3 months after discharge	(4) A history of lung volume reduction surgery within 3 months before admission;	
(5) Use of an Ellipta, pMDI, or soft mist inhaler (SMI) as the inhalation device	(5) Severe diseases, such as heart, liver, kidney diseases, or hemodynamic instability	
(6) Provision of written informed consent	(6) Currently pregnant, breastfeeding, or planning to become pregnant during the study	

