### Randomization, allocation concealment, and blinding

2.3

All patients will be randomly allocated at a 1:1 ratio to either the VIT or TIE group by using a random number table generated by an independent statistical analyst with SPSS. In accordance with the 2025 WHO age classification, participants will be stratified into two age groups (40–65 years and 66–85 years) before randomization to ensure balanced distribution across intervention arms. The assignment details will then be sealed in opaque envelopes. After each participant provides written informed consent and completes their baseline assessments, the study coordinator will open the envelope to reveal the participant's group allocation.

Because of the nature of the intervention, neither the participants nor the instructors will be blinded; nevertheless, the outcome assessors and statistical analysts will remain blinded to group assignments.

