(a) Inhalation flow rate evaluation: This will be performed using a portable pressure-flow measurement device (OHM-50; ORANGER DTx, Tianjin, China). While seated, the patient will use a special mouthpiece identical to the one in their regular inhalation device, as selected by the evaluator. The patient will be instructed to inhale as they normally would when taking their medication. The test will be repeated three times, and the best result will be recorded for further analysis. This evaluation will include three objective measures: PIFr, effective inspiratory time (EIT), effective inspiratory volume, and integrated inspiratory flow system (IIFS) score (IIFSs). EIT is the duration over which the inspiratory flow rate remains within the correct range during the PIFr test. EIV, representing the inhaled volume during the EIT, is determined by calculating the area under the inspiratory flow curve within the EIT. IIFS is a standardized scoring system based on objective data. IIFSs, calculated by comparing the measured inspiratory parameters with a standardized model, is a percentile-based score on a 100-point scale, reflecting the overall effectiveness of the patient's inhalation performance.

(b) Inhalation operation checklist: This will require the use of a medication-free inhaler canister equipped with an inhalation sensor for simulation. The patient will be asked to perform three simulated inhalations. The evaluator will observe the patient's inhalation steps and then record the results on the checklist by using the sensor's feedback. See Attachment 2 for the significance of the sensor feedback and the inhalation operation checklist. The entire process will be video recorded for future reference and review.

(5) Lung function: This will be assessed through spirometry using automated equipment as indicated in the guidelines.

(6) Physical fitness:

(a) 6-Min walk test: This test will be performed according to the recommendations of the European Respiratory Society/American Thoracic Society (21).

(b) Grip strength: This will be assessed bilaterally using a dynamometer (Jamar Plus+ Digital Hand Dynamometer, Fabrication Enterprises Inc, USA).

(c) Maximum voluntary contraction of knee extension: This will be measured using a handheld dynamometer (MicroFET 2; Hoggan, West Jordan, UT, USA).

(d) Respiratory muscle function: This will be assessed based on maximal inspiratory and expiratory pressures by using a Gio Digital Pressure Gauge (22).

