## Discussion

3

Inhaler technique is complex. Even after receiving appropriate education, many patients may use incorrect inhalation techniques due to a lack of detailed assessment of their equipment; this may reduce the efficacy of inhaled medications. Studies thus far have primarily observed the inspiratory flow rate in patients using DPIs to assess and guide optimization of inspiratory flow rate (18); however, research on the inspiratory flow rate in patients using pMDIs or SMIs is limited. We observed that when using a pMDI or SMI, most patients exhibited excessively high PIFrs (>80 L/min), increasing medication deposition in the oropharynx and thereby hindering effective drug delivery. Studies have reported that the error rate in inhalation techniques with pMDIs is as high as 86.7%, whereas that with SMIs is 58.9%. TIE primarily involves demonstration-based teaching: a physician first demonstrates the correct technique and key points to their patient; then, the patient mimics the technique under the physician's observation and guidance. However, with this technique, errors related to hand–mouth coordination and effective inhalation duration often remain undetected.

In this study, we will use sensors to monitor inhalation duration and hand–mouth coordination dynamically. With sensor feedback, physicians can provide targeted practice to address patient errors, overcoming the limitations of traditional education methods. To the best of our knowledge, this will be the first clinical study to objectively assess the entire inhalation process and offer targeted guidance for error correction. This will also be the first study to apply a visual method for inhalation technique instruction for patients with AECOPD. Visual feedback-based educational training methods have been widely applied in rehabilitation, with successful outcomes srehabilitation (24, 25), as well as in rehabilitation for pediatric cerebral palsy (26), orthopedic (27), and pain management (28).

Here, we primarily aim to observe and compare the impacts of our short-term VIT and the TIE on AECOPD frequency within 12 weeks after discharge. We anticipate that our results will provide evidence supporting the establishment of more effective inhaler technique education processes.

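### PIFr has device-specific targets but is compared raw across all inhalers, so its between-arm difference depends on device mix and cannot be read as benefit

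*Protocol article*

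**What the plan says.** Protocol article, Section 2.5.2, item (4)(a), lists PIFr with effective inspiratory time (EIT), effective inspiratory volume (EIV) and the integrated inspiratory flow system score (IIFSs). Patients inhale as they usually would, through a mouthpiece matched to their device: "The test will be repeated three times, and the best result will be recorded for further analysis". EIT is the time spent in the correct flow range, EIV is the volume inhaled in that time, and IIFSs compares the effort with a standardized model. PIFr itself is given no reference value in this section.

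The Background states that "an improper inspiratory flow rate—too low or too high—can hinder drug delivery". It gives one target for DPIs, "The optimal inspiratory flow rate for DPIs is approximately 60 L/min", and another for pMDIs and SMIs, which "thus have an optimal inspiratory flow rate of about 30 L/min". The Discussion adds that with a pMDI or SMI "most patients exhibited excessively high PIFrs (>80 L/min), increasing medication deposition in the oropharynx".

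Table 2 admits all these device classes: "Use of an Ellipta, pMDI, or soft mist inhaler (SMI) as the inhalation device". On allocation, Section 2.3 says "participants will be stratified into two age groups"; device is not a stratification factor. Section 2.7 assigns continuous variables to an independent-samples t-test, or to a Mann–Whitney test if assumptions fail. It mentions no device term or stratum.

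**The concern.** A two-sample comparison of a raw measurement is informative when a shift in one direction means the same thing for every patient. By the protocol's own account that is not so for PIFr. A fall is progress for a pMDI or SMI user at 80 L/min. A rise is progress for a DPI user below 60 L/min. If the devices are pooled, the two movements offset each other to a degree set by the share of each device, which the design leaves to recruitment.

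The recording rule adds to this. *Best* could mean highest or closest to target, and the text does not say which. For a pMDI or SMI user above 30 L/min, the highest effort is the one furthest from target.

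What is at stake is the reading of one secondary measure that the intervention trains directly. A null or shifted PIFr result could not be told apart from a change in device mix.

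**Working it through.** **Inputs from the protocol article.** Targets: 60 L/min (DPI) and 30 L/min (pMDI/SMI), from the Background. Untrained pMDI/SMI flow: above 80 L/min in most patients, from the Discussion; 80 is used below. Evaluable patients: 32 per group; recruited: 40 per group, both from Section 2.8. The protocol reports no PIFr result, SD or power, so there is no stated PIFr figure to reproduce.

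**Assumptions.** Ellipta is treated as the DPI in the device list; the text does not say so outright. The DPI baseline, the within-device SD and the device shares are not given and are assumed.

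**Step 1: the protocol's own flows, full success.** Let w be the DPI share and b the assumed untrained DPI flow. If every trained patient reaches target and controls stay untrained:

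raw difference = w(60 − b) + (1 − w)(30 − 80) = w(60 − b) − 50(1 − w).

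This is zero when w = 50 / (50 + 60 − b):
- b = 30: 50/80 = 62.5%
- b = 40: 50/70 = 71%
- b = 50: 50/60 = 83%

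For b = 30 the raw difference by DPI share is −50 (0%), −10 (50%), 0 (62.5%), +10 (75%) and +30 L/min (100%). Across the same mixes, mean distance from target in controls is 30w + 50(1 − w), which runs from 50 down to 30 L/min. It is 0 in the trained arm every time. The same complete success thus gives a raw result anywhere from −50 to +30.

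**Step 2: a milder illustration.** Assumed means, visual instruction (VIT) against traditional education (TIE): 60 vs 45 in Ellipta users and 40 vs 65 in pMDI/SMI users; SD 15; 32 per arm.

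raw difference = 15w − 25(1 − w).

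Power below is from simulated trials with a two-sided 5% t-test.

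| Ellipta share | Raw difference (L/min) | Raw power | Gain in distance from target (L/min) | Power, distance |
|---|---|---|---|---|
| 30% | 4.5 − 17.5 = −13 | 83% | 16 | >99% |
| 50% | 7.5 − 12.5 = −5 | about 20% | 13 | 97–98% |
| 62.5% | 9.375 − 9.375 = 0 | 5% | 11 | 93% |
| 90% | 13.5 − 2.5 = +11 | 76–77% | 7 | 67–68% |

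The Mann–Whitney test does not help: at 62.5% it also rejects in about 5% of trials, because ranks pool the devices just as means do.

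**Step 3: no cancellation.** Suppose Ellipta controls already average 60 and pMDI/SMI users go from 80 to 40. At 62.5% Ellipta the raw difference is 0.375 × (40 − 80) = −15 L/min, with about 92% power against 90% for distance. Nothing offsets here, but the size of the raw difference is still set by the pMDI/SMI share.

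**Step 4: the recording rule.** If *best* were read as highest, a patient whose efforts centre on 30 L/min would be recorded on average at 34, 38 or 43 L/min for an assumed within-patient SD of 5, 10 or 15. If it means closest to target, the recorded value averages 30.

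**The case against.** The article is a condensed account and refers to a preestablished analysis plan that is not shown; that plan may handle PIFr by device. No sentence says in terms that PIFr will be pooled raw. This limits the point to what is printed. But the article does state both the recording rule and the test, and as stated they do not suit the targets it gives.

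Other parts of the objection stand in full:
- Opposite movement is documented on one side only. No baseline flow is given for Ellipta users, so cancellation is an assumption, and an exactly null result needs a particular mix and particular means.
- Raw power is poor only near the cancelling mix. At 90% Ellipta the raw test does better than the distance measure.
- *Best* is undefined. It is not stated to be the highest, and closest to the standard is a fair reading of a protocol that treats flows above 80 L/min as excessive.
- Randomization without device strata does not bias the comparison.

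A reader might infer that the trial would report successful training as harm. That needs a higher-is-better reading, which the protocol never makes and which its Background and Discussion contradict for pMDI/SMI. A reader might also infer that the trial loses its main objective evidence of changed technique. The article does not rank PIFr first: EIT, EIV, IIFSs and a sensor-based checklist sit beside it. Because EIT and EIV are tied to a correct range and IIFSs to a standard model, nothing here calls for device terms in their analysis.

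**Conclusion.** The point holds in limited form. As written, the between-arm difference in raw PIFr has no fixed direction of benefit, and its size and sign depend on device mix. Under the assumed means it moves from −13 to +11 L/min as the Ellipta share goes from 30% to 90%, passing through zero at 62.5%, while distance from target improves by 7 to 16 L/min throughout. Those figures rest on an assumed DPI baseline below target, an assumed SD of 15 and the inference that Ellipta is a DPI. The dependence of the difference on device mix does not need the low DPI baseline, as Step 3 shows. The undefined *best* is a second, smaller gap in the same measure.

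This concerns one component of one secondary outcome. The primary outcome, exacerbation frequency over 12 weeks, is untouched. The change is worth making because it is cheap, not because the trial's main conclusion is at risk.

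**What to change.** State in the analysis plan, before outcome data are examined, that:
- PIFr is analysed as absolute distance from the device-specific target, or as in or out of the device-specific correct range already needed to compute EIT, adjusted for device class and baseline PIFr;
- *best* means the effort closest to the device target, or else the mean of the three efforts is used;
- raw PIFr is reported only within device class.

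The cost is wording and a little more analysis work. Device type is known from eligibility, PIFr is measured at baseline, and three efforts are already made; all three values need to be kept. The price in power is real if nearly all patients use one device: at 90% Ellipta the distance measure had about 67–68% power against 76–77% for raw PIFr in the illustration. Within-class reporting of raw PIFr partly covers that case.

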(7) Chronic activity-related dyspnea: This will be assessed using the modified Medical Research Council dyspnea scale.

(8) Inhaler medication adherence: The Chinese version of the Test of Adherence to Inhalers (TAI) will be used to assess treatment adherence. TAI scores, ranging from 10 to 50, are used to categorize adherence into three levels: low (≤45), moderate (46–49), and high (50). This scale has good reliability and validity (23).

(9) Health-related quality of life: This will be measured using the COPD Assessment Test.

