### Statistical analysis

2.7

Data analysis will follow the modified intention-to-treat principle to ensure complete randomization, minimize selection bias, and reflect real clinical practice. Missing data will be addressed using multiple imputation to reduce potential bias resulting from missing information, ensuring the robustness and accuracy of the analysis. All statistical tests will be performed according to a preestablished statistical analysis plan. SPSS (version 21.0) will be used for all data analyses, and two-tailed *p* < 0.05 will be considered to indicate statistical significance.

Continuous variables will be expressed as means ± standard deviations or median (Interquartile) where appropriate, and categorical variables as frequencies and percentages. Normality testing for continuous variables will be performed using the Shapiro–Wilk or Kolmogorov–Smirnov test, and homogeneity of variance will be assessed using the Levene test. For continuous variables that are normally distributed with equal variance, intergroup comparisons will be conducted using the independent-samples *t*-test. For continuous variables that do not meet the normality or homogeneity assumptions, the Mann–Whitney *U*-test will be employed. For discrete variables (such as the AE number and severity over 12 weeks), intergroup comparisons will be performed using the chi-square, Fisher exact, or Cochran–Mantel–Haensel χ^2^ test.

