### Sample size calculation

2.8

Our literature review indicated that the AE rate within 3 months after hospitalization for AECOPD is approximately 48.9% (5). Our preliminary data (unpublished) indicate that after VIT, the treatment failure rate at 90 days is approximately 15%. Therefore, the expected effect size between the two groups is about 33.9%. We set the significance level α = 0.05 and the statistical power at 80% (i.e., β = 0.20), with a dropout rate assumed to be 20%. The calculated values for *Z*_α_/2 and *Z*β are 1.96 and 0.84, respectively, with standard deviation σ = 0.614, effect size Δ = 0.339. Based on these parameters and sample size calculations, each group must include ≥32 patients. To ensure data accuracy and account for potential dropouts, we plan to recruit 40 patients per study group, totaling 80 participants.

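### Inhaler adherence (TAI, 10–50) is defined only through three levels; analysing the week-12 score with the V0 score would avoid a possible loss of power

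*Protocol article*

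**What the plan says.** Section 2.5.2, item (8), names inhaler adherence as a secondary outcome measured with the Chinese TAI, and continues: "TAI scores, ranging from 10 to 50, are used to categorize adherence into three levels: low (≤45), moderate (46–49), and high (50"). It then says that the scale is reliable and valid. It gives no reason for comparing levels and does not say whether the score or the level is compared between arms. Table 1 schedules the TAI at V0 and again at V3, week 12 after discharge.

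Section 2.7 sorts variables by type and does not mention the TAI.
- Normally distributed continuous variables with equal variance go to the independent-samples t-test. For the rest: "For continuous variables that do not meet the normality or homogeneity assumptions, the Mann–Whitney *U*-test will be employed".
- Discrete variables are introduced by example, "For discrete variables (such as the AE number and severity over 12 weeks"), and for these "intergroup comparisons will be performed using the chi-square, Fisher exact, or Cochran–Mantel–Haensel χ^2^ test".
- Details are deferred: "All statistical tests will be performed according to a preestablished statistical analysis plan".

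The significance rule is "two-tailed *p* < 0.05 will be considered to indicate statistical significance". Section 2.8 sizes the trial on the primary outcome only. It gives no effect, SD, distribution or power for the TAI.

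**The concern.** The three levels are the only form in which the outcome is described. The Abstract names a score for dyspnea and for quality of life, but for adherence it names only adherence itself. AE severity, which section 2.7 gives as an example of a discrete variable, is also a three-level ordered grade (mild, moderate, severe). The natural reading is therefore that low, moderate and high adherence would be compared with the same tests.

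That reading has three costs:
- The cut discards information. Week-12 scores of 20 and 45 fall in the same level, while 45 and 46 do not.
- Chi-square and Fisher ignore the order of the levels.
- No between-group test in section 2.7 is said to use the V0 score, although every patient is scheduled to have one.

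Adherence matters for interpretation. Patients are not blinded (section 2.3), and a difference in adherence would be a rival explanation for a difference in exacerbations. A coarse comparison is less likely to show such a difference if it exists.

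**Working it through.** **Inputs from the article.** TAI range and cut-points (2.5.2(8)); two-sided 0.05 (2.7); at least 32 patients per group, 40 recruited (2.8).

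**The article's own figure.** Section 2.8 concerns the primary outcome and is used here only for the arm sizes. The stated σ follows from the two rates: √(0.489 × 0.511 + 0.15 × 0.85) = √0.377 = 0.614. Then n = ((1.96 + 0.84) × 0.614 / 0.339)² = 25.7. Allowing for 20% dropout, 25.7 / 0.8 = 32.1, which matches the stated 32; 32 / 0.8 = 40. There is no TAI figure to reproduce.

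**Coarseness of the levels.** Scores 10 to 50 give 41 values. Low (10–45) holds 36, moderate (46–49) holds 4 and high (50) holds 1: 36 + 4 + 1 = 41.

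**Assumptions, not in the article.** TAI scores are normal, rounded and capped to 10–50. Control mean/SD before capping is 40/6, 43/5, 46/4, 47.5/3, 48/4 or 49/4. The VIT arm is shifted by 0.5, 0.7 or 0.8 SD. Each scenario has 4,000 simulated trials, so the simulation error of a power is at most √(0.25/4000) = 0.8 points.

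**Power (%) at 32 per arm, shift 0.7 SD:**

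| Control mean/SD | Controls at low level | Mann–Whitney, score | Chi-square, levels | Fisher, levels | Ordinal CMH-type, levels |
|---|---|---|---|---|---|
| 40/6 | 82 | 76.9 | 47.1 | 46.0 | 56.9 |
| 43/5 | 69 | 74.8 | 53.9 | 53.0 | 64.1 |
| 46/4 | 45 | 72.8 | 57.4 | 55.9 | 69.8 |
| 47.5/3 | 25 | 72.8 | 57.6 | 56.6 | 69.2 |
| 48/4 | 26 | 67.4 | 55.5 | 54.5 | 65.2 |
| 49/4 | 19 | 65.7 | 53.6 | 52.2 | 64.6 |

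Loss = Mann–Whitney power minus the power of the test on levels. For 46/4 with chi-square it is 72.8 − 57.4 = 15.4 points.

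**Loss over all scenarios (32 and 40 per arm, all shifts):**
- Chi-square: 8.4 to 29.8 points.
- Fisher: 9.7 to 30.9 points.
- Ordinal CMH-type test: 0.8 to 20.0 points. This splits into 0.8–4.7 when the control mean is 46 or more, 6.3–10.8 at 43/5 and 13.6–20.0 at 40/6.

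**How much is due to the cut, and how much to ignoring order.** A second set of runs used control mean/SD 44/6, 46/5, 48/5 and 42/7 and a 0.65 SD shift. Powers at 32 per arm for Mann–Whitney on the score, Mann–Whitney on the levels and chi-square on the levels were:
- 44/6: 68.8, 61.6, 51.8
- 46/5: 66.3, 63.2, 51.8
- 48/5: 63.2, 61.3, 50.0
- 42/7: 67.5, 56.2, 47.1

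The cut alone costs 7.2, 3.1, 1.9 and 11.3 points. Chi-square costs 17.0, 14.5, 13.2 and 20.4 in total. At 40 per arm the totals are 17.2, 13.8, 11.0 and 22.4. Rejection rates under no difference were 4.3–6.1%, so the differences in power do not come from an inflated error rate.

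**Not quantified.** The gain from including the V0 score depends on the V0–V3 correlation, which the article does not give.

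**The case against.** The strongest reply is that nothing in the article commits the TAI to a test on levels. The sentence in 2.5.2(8) may only describe how the instrument is scored, as item (1) does for EXACT-Pro. Section 2.7 also provides a t-test or Mann–Whitney for a numeric score, and on that reading the loss is zero. The form of one secondary outcome could properly be settled in the separate analysis plan. This stands: the routing to tests on levels is an inference, and the point has to be conditional.

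The second reply is that the list of tests includes CMH, whose ordinal form recovers most of the loss when scores are high. This also stands in part. Section 2.7 does not say which form of CMH is meant, what its strata would be, or how to choose among the three tests. Even the ordinal form loses 6 points or more when most controls score 45 or less.

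The third reply is that the consequence should not be pressed. The article nowhere plans to use a TAI test to rule out adherence as an explanation. A non-significant result could not do so even on the score. The weekly calls and reminders go to both arms (2.4, 2.6), so a shift of 0.5–0.8 SD may be optimistic. This stands: the gain is in precision for a supporting outcome.

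What remains is that levels are the only form given for the outcome, and that no between-group test is said to use a V0 score already collected.

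**Conclusion.** The point holds as a low-cost improvement, not as an error. If the three levels are compared with unordered chi-square or Fisher, power falls by roughly 8–31 points against a rank test on the score. With an ordinal CMH-type test the loss is about 1–20 points, mostly 1–5 when the control mean is 46 or more. With the score itself there is no such loss. All of these figures rest on assumed TAI distributions and shifts.

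A reader might infer that section 2.7 assigns the TAI to chi-square or Fisher and that a definite amount of power, such as 13–22 points, is lost. The article does not support this. Section 2.7 never names the TAI, it also lists CMH, and it leaves a comparison of scores open. That range is not a bound either: the chi-square loss was as low as 8 points and as high as 30. Nor is the cut itself the main cause in most of the second set of runs. It accounts for about 2–11 points, and in three of the four scenarios the larger share comes from ignoring order. No stated sample size or power is wrong on this account, since the trial is not powered on the TAI.

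**What to change.** In 2.5.2(8), state that the analysed adherence outcome is the TAI total score at week 12. In 2.7, state that arms are compared with a rank-based or proportional-odds model that includes the V0 TAI score. Such a model copes with the ceiling at 50. Keep the three levels as a descriptive table. If a test on them is kept, specify an ordinal (trend) test in place of chi-square or Fisher.

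The cost is a sentence or so in each section. No new data, visits or patients are needed, because Table 1 already schedules the TAI at V0 and V3. The small downside is that a shift in score is slightly less familiar to clinicians than adherence levels, which remain in the descriptive table.
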